## Abstract

**Graphical Abstract:**

Flow diagram of the ENABLE-Hip trial (ClinicalTrials.gov Identifier: NCT06611319).

ERAS: enhanced recovery after surgery; *o.d*.: *omni die* (once daily).

[figure not shown]

## Highlights

The number of patients requiring a surgical joint arthroplasty is constantly increasing.ENABLE-Hip is a rage multicenter multinational randomized trial testing the hypothesis that a shorter duration of anticoagulant treatment is non-inferior to the current standard of care in preventing symptomatic or fatal venous thromboembolism in patients after hip arthroplasty.The trial will inform future national and international guidelines for this large and continuously growing patient population, and may improve patient care by reducing the need for anticoagulation and its associated complications.

## Introduction

An increasing proportion of the ageing population in Europe and other parts of the world suffers from osteoarthritis and will need joint arthroplasty at some time in their lives. In the United States, more than one million total joint arthroplasty procedures are performed each year [1]. In Europe, an analysis of the German nationwide inpatient statistics revealed that the annual number of patients undergoing total hip arthroplasty (THA) increased from 145,223 in the year 2005 to 171,421 in 2016 [2]. THA is a surgical procedure with a high risk of venous thromboembolism (VTE). Early data reported postoperative VTE rates, including asymptomatic deep vein thrombosis (DVT), as high as 84% without thromboprophylaxis [3]. As a result, experts and guidelines recommend pharmacologic VTE prophylaxis as the standard of care [4–8]. However, the VTE risk and consequently the appropriate duration of anticoagulation may vary, depending on advances in surgical techniques, the speed of postoperative mobilization, and the length of hospital stay. In this context, improved surgical techniques and early recovery protocols (so-called *fast-track* surgery) may help to reduce the incidence of postoperative VTE [9, 10]. To achieve this goal, enhanced recovery programs have been developed and are increasingly implemented in the surgical treatment of knee and hip osteoarthritis. An interdisciplinary team of orthopaedic surgeons, anesthesiologists, nurses and physiotherapists involves the patient as an active member of the perioperative management with the aim of promoting early postoperative mobility and reducing morbidity and the length of hospital stay [11].

The appropriate duration of anticoagulation following elective THA is a controversial, dynamically evolving topic. Country-specific recommendations and physician as well as patient preferences have a major impact on postoperative management with regard to thromboprohylaxis. For example, in Germany, interdisciplinary guidelines last updated in 2015 [12], advocate the administration of a low-molecular weight heparin (LMWH), fondaparinux, or an approved direct oral anticoagulant (DOAC) at a prophylactic dose for 28–35 days after THA. In contrast, in North America, both older [6, 7] and updated recommendations encourage acetylsalicylic acid (ASA) prescriptions by orthopedic specialists [8].

Over the last ten years, a number of studies compared various thromboprophylaxis regimens in patients after a hip or knee arthroplasty. Two of them need particular mentioning due to their design and their size:

A large multicenter double-blind randomized controlled trial (RCT) involving 3,424 patients (1,804 undergoing THA and 1,620 undergoing total knee arthroplasty, TKA) was conducted in Canada. Among patients who received 5 days of postoperative rivaroxaban, extended prophylaxis with ASA was not significantly different from continued rivaroxaban in the prevention of symptomatic VTE; primary event rates were low (≤ 0.70%) in both treatment arms [13]. Of note, the mean length of hospital stay was short (< 4 days) in that trial; this is still in contrast to clinical practice in some European countries, in which postoperative stay is generally longer [2], approaching 4 days only in selected centers [11]. Moreover, although major bleeding complications were infrequent in both groups, they were numerically more frequent (8 versus 5) in the ASA compared to the standard anticoagulation group [13], generating questions on whether there is any clinically relevant benefit by replacing an anticoagulant with ASA.

More recently, a cluster-randomized, crossover, registry-nested trial across 31 hospitals in Australia examined whether ASA was non-inferior to enoxaparin in preventing symptomatic VTE after THA or TKA [14]. Enrollment was stopped after an interim analysis determined the stopping rule was met, with 9,711 of the prespecified 15,562 patients enrolled (62%); of those, 9,203 (95%) completed the trial. Within 90 days of surgery, the symptomatic VTE rate in the ASA group was 3.45% compared to 1.82% in the enoxaparin group (estimated difference, 1.97%; 95% CI, 0.54%-3.41%). This failed to meet the non-inferiority criterion for ASA, being significantly superior for enoxaparin (P = 0.007) [14]. Currently, the ongoing Extended Venous Thromboembolism Prophylaxis Comparing Rivaroxaban and Aspirin to Aspirin Alone Following Total Hip and Knee Arthroplasty (EPCAT) III trial (NCT04075240) is comparing 35 days of ASA (without an anticoagulant) with 5 days of rivaroxaban followed by 30 days of ASA in patients undergoing THA.

In view of the existing data, it has been proposed to limit anticoagulation to the in-hospital period after *fast-track* THA and discontinue it upon discharge without replacement by an antiplatelet agent; in fact, the positive results of cohort studies performed in Denmark [10, 15] led to an endorsement of short, in-hospital-only thromboprophylaxis in that country [16]. Nevertheless, broader acceptance of this approach necessitates robust, large-scale controlled data [17–21].

### Study design and objectives

ENABLE-Hip (ClinicalTrials.gov Identifier: NCT06611319) is an academic prospective randomized double-blind active-control non-inferiority trial. Sponsor is the University Medical Center of the Johannes Gutenberg University, Mainz, Germany. The trial tests the hypothesis that a *shorter duration* of anticoagulant treatment is non-inferior, in terms of preventing symptomatic or fatal VTE, compared to the current standard of care. Specifically, a regimen of short (over 10 days) prophylactic anticoagulation, postulated to be effective and safe after fast-track THA on the basis of existing data as mentioned above, will be compared to standard-duration (35 days) anticoagulation as per current guidelines. The double-blind design will minimize the risk of unjustified diagnostic work-up (particularly for DVT) in patients without new-onset symptoms in the experimental arm, and participating investigators will be advised to adhere to guideline recommendations in this regard [22, 23].

### Patient population and eligibility

Adult patients, aged 18 to 85 years, undergoing elective unilateral primary THA, who fulfill the criteria for enhanced (fast-track) recovery based on a predefined multidisciplinary plan of care will be included in the ENABLE-Hip trial [11]. The key inclusion and exclusion criteria are listed in Table 1.

**Table 1 Tab1:** Key inclusion and exclusion criteria

Inclusion criteria	Exclusion criteria
1) Written informed consent 2) Age between 18 and 85 years 3) Scheduled to undergo elective unilateral primary THA and eligible for perioperative management based on the ERAS protocol 4) Baseline TUG test scoring < 20 s, corresponding to a good mobility status before surgery 5) Capability to understand and comply with the protocol requirements (e.g., to answer the questionnaires) 6) Negative serum pregnancy test and and highly effective method of contraception for the duration of study treatment	1) Previous DVT or PE 2) Hip or lower limb fracture in the previous three months 3) Major surgical procedure within the previous three months 4) Active cancer (metastatic or requiring chemotherapy or radiation therapy) 5) Active peptic ulcer disease, gastritis, or prior gastrointestinal bleeding 6) Obesity with body mass index (BMI) > 40 kg/m^2^ body surface area 7) Severe renal impairment defined as estimated glomerular filtration rate < 30 ml/min 8) Severe hepatic impairment defined as Child Pugh Class B or C 9) Uncontrolled intercurrent illness (i.e., active infection, symptomatic congestive heart failure, uncontrolled hypertension, unstable angina pectoris, interstitial lung disease, serious gastrointestinal conditions, psychiatric illness) 10) Active or recent major bleeding at any site, or any disease or condition which, in the investigator’s jedgement, may significantly increase the bleeding risk during postoperative anticoagulation 11) Contraindication to discharge within 6 days after surgery 12) Expected requirement for major surgery within a 90-day period post THA 13) Need for long-term anticoagulation (e.g., atrial fibrillation, previous VTE) 14) Need for chronic antiplatelet therapy except for acetyl salicylic acid at a dose ≤ 100 mg daily or clopidogrel 75 mg daily 15) Previous participation in this trial 16) Life expectancy < 6 months 17) Participation in another interventional clinical trial at inclusion or within the last 30 days prior to inclusion, except during the observational follow-up period of that rial 18) History of hypersensitivity to the investigational medicinal product or to any drug with similar chemical structure or to any excipient in its pharmaceutical form

DVT: deep vein thrombosis; ERAS: enhanced recovery after surgery; PE: pulmonary embolism; THA: total hip arthroplasty; TUG: Timed Up and Go; VTE: venous thromboembolism

Informed consent by the participants will be necessary for documentation and evaluation of their data. Subjects can withdraw their consent at any time during the trial and without giving reasons, and this will not entail any disadvantages for them. If possible, subjects having withdrawn consent will be followed, and all examinations scheduled for the end-of-study visit will be performed and documented for inclusion in the statistical analysis.

### Intervention and treatment regimens, trial flow

In the experimental intervention arm, patients will be mobilized early after THA surgery, following the standardized Early Recovery After Surgery (ERAS) protocol [11]. Following a brief initial open-label period of prophylactic anticoagulation (to allow for subcutaneous low molecular weight heparin if mandated by local treatment protocols) until day 2 after surgery, treatment with the study drug (rivaroxaban at the standard, approved prophylactic oral dose of 10 mg once daily) will be started on the third postoperative day and continued for 8 days (i.e., until day 10 after surgery). After this time, patients will be switched (in a double-blinded manner) to placebo, to be continued for 25 days (until day 35 after surgery).

In the control arm, patients will follow the same standardized enhanced recovery protocol as the experimental group. Following a brief initial open-label period of prophylactic anticoagulation as per local standard of care (to allow for subcutaneous low molecular weight heparin if mandated by local treatment protocols) until day 2 after surgery, treatment with the study drug (rivaroxaban at the standard, approved prophylactic oral dose of 10 mg once daily) will be started on the third postoperative day and continued for 8 days (i.e., until day 10 after surgery). After this time, patients will continue (in a double-blinded manner) to receive rivaroxaban at the above mentioned dose for 25 days (i.e., until day 35 after surgery).

The trial flow diagram is shown in Graphical Abstract. After confirmation of eligibility criteria (Table 1) and obtaining written informed consent, subjects will be randomly assigned to one of the above treatment groups. Treatment assignment will be performed via the electronic case report form (eCRF) on Visit 1 (day -10 to day -1 before surgery). A randomization/treatment assignment list will be generated by the Institute of Medical Biostatistics, Epidemiology and Informatics (IMBEI) at the University Medical Center Mainz. The randomization ratio of the experimental treatment group and the control treatment group will be 1:1. In order to account for possible differences in the initial open-label period of prophylactic anticoagulation as per local standard, randomization will be performed per site. Additionally, randomization will be stratified by concomitant single chronic antiplatelet medication (ASA or clopidogrel). Block randomization with varying block length will be applied. Considering that 10–15 centers are expected to recruit a total of 2,932 patients into the trial (see below), we anticipate 20 strata with sizes between 100 and 150.

### Outcomes

The trial visit plan is displayed in Table 2; the primary and secondary endpoints are described in Table 3. The primary efficacy endpoint is acute symptomatic or fatal VTE, defined as (i) symptomatic DVT of the popliteal or more proximal leg veins (femoral or iliac veins) or inferior vena cava; or (ii) symptomatic (segmental or more proximal) or fatal PE, occurring within the first 90 days after surgery and confirmed by objective testing. Physicians will be advised to use standardized clinical prediction rules and diagnostic algorithms for *clinically suspected* VTE as recommended by current guidelines [22, 23]. Patients with suspected DVT will undergo compression sonography from the common femoral vein to the trifurcation of the popliteal vein. Patients with suspected PE will undergo computed tomography pulmonary angiography or ventilation-perfusion lung scan or invasive pulmonary angiography. No screening or diagnostic tests will be performed in asymptomatic patients.

**Table 2 Tab2:** Trial visit plan and data collection schedule

Visits	Visit 1 (Screening and Enrolment)	Visit 2 (Surgery)	Visit 3 (Discharge)	Visit 4 (EOT)	Visit 5 (EOS)
Action					
Trial day	Day-10 to -1	Day 0	Day 2–6	Day 35 (+ 7 days)	Day 90 (± 10 days)
Type of visit	On site	In hospital		Telephone contact	On site
Demographics (e.g., sex, age)	X				
Subject information and written informed consent	X				
Medical history	X				
Inclusion/exclusion criteria	X				
Physical examination^a^	X		X		X
Vital signs^b^	X		X		
Clinical chemistry^c^	X				
Hematology^d^	X				
Serum pregnancy test^e^	X				
Dispense of urine pregnancy test^e^			X		
Urine pregnancy test^e^				X	
Range of motion (active)	X		X		X
Timed Up and Go (TUG) score	X		X		X
Allocation of study medication and patient number via eCRF	X				
Patient questionnaires					
• Hip disability and Osteoarthritis Outcome Score (HOOS-12)	X				X
• EQ-5D-5L (generic quality of life)	X				X
• Health care resources utilization				X	
Dispense of study medication^f^		X	X		
Observation and documentation of					
• Symptomatic/fatal venous thromboembolism^g^		X	X	X	X
• Major and clinically relevant non-major bleeding		X	X	X	X
• Stroke (haemorrhagic/ischemic)		X	X	X	X
• Other Adverse Events (AEs)	X	X	X	X	X
• Concomitant medication/therapies	X	X	X	X	X
End of trial (final visit)					X

EOS: end of study; EOT: end of treatment

^a^Examination regarding signs of orthopnea, moist rales/pulmonary edema, distended neck veins and leg vein thrombosis

^b^Blood pressure, pulse rate, respiratory rate, arterial or capillary blood oxygen saturation, body temperature

^c^Sodium, potassium, calcium, magnesium, chloride, glucose, creatinine, estimated glomerular filtration rate (eGFR), alanine aminotransferase (ALT), γ-glutamyltransferase (γ-GT), international normalized ratio (INR), activated partial thromboplastin time (aPTT)

^d^Leukocyte (total white blood cell count, basophils, eosinophils, neutrophils, monocytes, lymphocytes), erythrocyte and platelet count, hemoglobin, hematocrit

^e^Required for women of childbearing potential (i.e., all women until 2 years post-menopausal)

^f^The study medication kit will be dispensed once, either at Visit 2 or Visit 3, but in any case, before or on day 3 after surgery

^g^Diagnostic work-up of clinically suspected deep vein thrombosis or pulmonary embolism as per current guideline recommendations (no screening in asymptomatic patients)

**Table 3 Tab3:** Primary and secondary endpoints

Primary endpoint	Secondary endpoints
Acute symptomatic or fatal VTE, defined as (i) symptomatic DVT of the popliteal or more proximal leg veins (femoral or iliac veins) or inferior vena cava; or (ii) symptomatic (segmental or more proximal) or fatal PE, occurring in the first 90 days after surgery and confirmed by objective testing Safety endpoint: Overt major or clinically relevant non-major bleeding	(1) Death from any cause (2) Isolated symptomatic distal DVT (3) Myocardial infarction or stroke (4) Need for readmission to the hospital (5) Length of hospital stay (6) Serious adverse events (SAEs) (7) Patient mobility (8) Changes in patient-reported hip joint-specific disability measured by the HOOS-12 score following surgery (9) Generic quality of life measured by EQ-5D-5L All within 3 months of the surgical intervention and using standardized scores and questionnaires Postoperative healthcare resource utilization will be assessed at 35 days after surgery

DVT: deep vein thrombosis; ERAS: Enhanced Recovery After Surgery (protocol); HOOS: Hip disability and Osteoarthritis Outcome; PE: pulmonary embolism

The safety endpoint is overt major or clinically relevant non-major bleeding. An overt bleed will be categorized as major if it fulfils at least one of the following criteria [24, 25]: (i) fatal; (ii) bleeding into a critical area or organ; (iii) surgical site bleeding that causes hemodynamic instability; (iv) non-surgical site bleeding causing a fall in hemoglobin level of ≥ 20 g L^−1^, or leading to transfusion of ≥ 2 units of whole blood or red blood cells; (v) surgical site bleeding that requires a second intervention (open, arthroscopic, endovascular), or hemarthrosis of sufficient size to delay mobilization or wound healing. Bleeding will be categorized as clinically relevant non-major if it does not meet the criteria for major bleeding, but results in hospitalization, aspiration of a wound, or a wound hematoma complicated by infection or any other non-major bleeding requiring medical attention. All other overt bleeding events will be considered minor.

Both the primary efficacy endpoint and the safety endpoint will be adjudicated by an independent critical events committee (CEC).

The EQ-5D-5L is a patient-reported outcome measure that provides a simple descriptive profile and a single index value for health status. The questionnaire entails 5 dimensions, including mobility, self-care, usual activities, pain/discomfort and anxiety/depression [26]. Patients will be asked to complete the questionnaire at baseline (Visit 1) and 90 days after surgery (Visit 5) (Table 2). The questionnaire will be administered at the beginning of the trial Visit, prior to any interaction with the trial investigator, including any tests, treatments or receipt of test/examination results. This is to avoid any possible influence on the subjects or their responses to the quality-of-life (QoL) questionnaire.

The Hip disability and Osteoarthritis Outcome Score (HOOS)-12, developed as a 12-item short form of the original 42-item HOOS [27], is one of the most widely used patient-reported outcome measures surrounding total hip arthroplasty [28, 29]. It assesses pain, function and quality of life. Patients will be asked to complete the questionnaire at baseline (Visit 1) and 90 days after surgery (Visit 5) (Table 2).

Utilization of health care resources will be recorded up to 35 days after surgery. Key parameters of health care resources utilization will be evaluated from a payers’ perspective and comprise visits to health care providers (general practitioner, medical specialists, etc.), rehospitalization as well as employment status and, if applicable, duration of inability to work (up to/more than 6 weeks) [30]. At Visit 3 (discharge), study participants will be asked to record all physician contacts/visits and medical treatments or healthcare services they received following discharge from the study site, and to provide relevant information at Visit 4 (at 35 days after surgery; Table 2).

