A sample size of 2,786 evaluable patients has been calculated. Taking into account a possible censoring (i.e., dropout) rate of 5%, 2,932 patients need to be included in the trial. The assumptions for calculating the sample size were based on largely consistent existing data. More specifically, a pooled analysis[31] of 14 randomized controlled trials cited by the American College of Clinical Pharmacy (ACCP) guidelines on VTE prophylaxis after orthopedic surgery [5], yielded a symptomatic DVT rate of 1.27% after prophylactic LMWH use. Data from a prospective database of hospital-acquired VTE after THA or TKA in the United Kingdom revealed a similar VTE (DVT or PE) rate of 1.11% [32]. Based on these data and on Canadian experience, a large randomized controlled trial on brief (5-day) postoperative anticoagulation followed by ASA versus standard-duration anticoagulation assumed a 3-month VTE probability of 1.0% in the standard-of-care arm [13]. Although that trial eventually found VTE in only 0.64–0.70% of the patients in either arm [13], a 1.0% probability in the control arm remains an appropriate estimate as the results of the other studies mentioned above appear to be supported by a registry on total joint arthroplasty in the United States [33]. For the experimental arm, the estimated rate of ≥ 2% as per **H**_**0**_ corresponds to a ‘minimal clinically significant difference’ of 1.0% compared to the standard of care. This margin is medically sensible, considering that approximately 1 out of 25 (post-THA) VTE events that *might* occur due to a shorter anticoagulation period may be life-threatening, which has to be viewed against an up to 10% expected case-fatality rate of major hemorrhage associated with (longer) anticoagulation (reviewed in [13]). Finally, the assumption of a low frequency (1.0% or even less) of VTE events as per H_1_ is justified by the results of a nationwide prospective Danish cohort study, in which anticoagulation treatment (not followed by ASA) was given for the duration of hospitalization if it was less than 5 days [15].

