The primary efficacy endpoint will be analyzed in the per-protocol (PP) population and in the modified intention-to-treat population (mITT). The PP population consists of all patients who have (i) signed the informed consent; (ii) undergone randomization and the planned surgical procedure (THA); and (iii) completed the study without major protocol deviations. The mITT population includes all randomized patients who underwent THA and received at least one dose of the study medication.

In case of poor protocol adherence, the duration of study treatment would be shortened similarly in both treatment arms (since this is a double-blind trial), and this would affect efficacy particularly in the control intervention arm in which active treatment duration is longer. On the other hand, if there were protocol violations leading to arbitrary discontinuation of study treatment and prescription of open-label rivaroxaban after day 10, these would happen with equal frequency in both groups, again given the double-blind design. Either scenario would result in attenuation or elimination of the differences in the ITT population, favoring demonstration of ‘non-inferiority’. For these reasons, testing for non-inferiority in the PP population is considered the most rigorous approach in such a setting [34, 35]. Nonetheless, as a European Medicines Agency (EMA) Reflection Paper suggests that the full analysis set (ITT) and the PP analysis set both have equal importance [36], the primary endpoint will be analyzed in both populations and non-inferiority will be declared if it can be established in both.

H_0_: p_E_–p_C_ ≥ δ, with δ = 0.01, where p_E_ and p_C_ are symptomatic VTE probability within 3 months in the experimental (p_E_) and control group (p_C_) respectively, will be tested against H_1_, p_E_–p_C_ < δ, with δ = 0.01. The test will be implemented by comparing the cumulative incidence of VTE at 3 months using the complementary log–log transformation [37]. Comparisons will be adjusted for stratum. Point estimates of the cumulative incidence will be obtained using the Kaplan–Meier method. To account for patients completing only part of the follow-up, tests based on the cumulative incidence will be used.

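### Absence from work of more than 6 weeks cannot be observed when it is asked about only at day 35 to 42; a lesser point is that the final visit may precede day 90

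*Protocol article*

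**What the plan says.** **Resource use.** In the protocol article, the Outcomes section sets the period: "Utilization of health care resources will be recorded up to 35 days after surgery". Participants are told at discharge to keep a record of their contacts and treatments and "to provide relevant information at Visit 4 (at 35 days after surgery; Table 2". Table 3 agrees: "Postoperative healthcare resource utilization will be assessed at 35 days after surgery". Table 2 marks the resource-use questionnaire at Visit 4 only, a telephone contact on day 35 with 7 days' allowance afterwards and none before. Visit 5 has no mark for it. The parameters to be evaluated from the payers' perspective include employment status and, for those to whom it applies, "duration of inability to work (up to/more than 6 weeks".

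**Primary endpoint.** The same section counts symptomatic or fatal VTE "occurring within the first 90 days after surgery and confirmed by objective testing". Table 2 sets Visit 5, the final visit, at day 90 with 10 days' allowance on either side. For incomplete follow-up, the statistical section states: "To account for patients completing only part of the follow-up, tests based on the cumulative incidence will be used".

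**The concern.** The work-incapacity item has two categories, but the only contact that collects it comes too early to tell them apart for absence beginning with the operation. A patient off work since surgery who is still off work at the call has an unfinished spell. If it is entered as up to 6 weeks, a spell that later runs longer is misclassified. If it is left open, the item has no value for the patients with the longest absence, who matter most to a payer. Either way the long category is under-counted in both arms, and a comparison of the arms on this item says little.

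The final visit raises a similar but much smaller timing question. A patient seen on time under Table 2, on any of days 80 to 89, leaves scheduled follow-up before the 90-day window has closed.

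**Working it through.** The plan gives no figure to reproduce here. The first check is calendar arithmetic on stated windows, and the second sizes a consequence under stated assumptions.

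**Work incapacity**

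- Cut-off (Outcomes): 6 weeks = 6 × 7 = 42 days.
- Stated recording limit (Outcomes, Table 3): day 35 = 35/7 = 5.0 weeks.
- Latest permitted Visit 4 (Table 2): 35 + 7 = day 42 = 6.0 weeks.
- Longest elapsed absence from surgery observable at Visit 4: 42 days. The upper category needs more than 42.
- Earliest permitted Visit 5 (Table 2): 90 − 10 = day 80, which is 80 − 42 = 38 days past the cut-off.

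So no permitted Visit 4 can show absence from surgery of more than 6 weeks, and every permitted Visit 5 could. Using the full 7-day allowance does not help, and data from after day 35 would already lie outside the stated recording period.

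**Final visit and the 90-day window**

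Inputs:
- control-arm rate of 1.0% ("a 1.0% probability in the control arm remains an appropriate estimate"), applied to both arms;
- sample size ("A sample size of 2,786 evaluable patients has been calculated"), which gives 2,786/2 = 1,393 per arm;
- Visit 5 window of day 80 to day 100.

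Assumption: a constant VTE hazard over 90 days. The article gives no event timing.

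- Worst case, every patient seen on day 80: 10 of 90 days unobserved (11%). Rate unobserved = 1.0% × 10/90 = 0.11 percentage points. Events = 1,393 × 0.0011 = about 1.5 per arm.
- Visits spread evenly over the 21 days from 80 to 100 (a second assumption): mean days lost = (10 + 9 + … + 1)/21 = 55/21 = 2.6. Rate unobserved = 1.0% × 2.6/90 = 0.03 percentage points. Events = 1,393 × 0.0003 = about 0.4 per arm.
- Events concentrated soon after surgery: the loss approaches 0.

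The effect on precision under an even (continuous) spread is also small. The fraction still observed falls linearly from 1 at day 80 to 0.5 at day 90, so the last 10 days contribute to the variance as if they were 20 × ln 2 = 13.86 days. The variance ratio is (80 + 13.86)/90 = 1.043, which raises the standard error by about 2%.

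**The case against.** **On work incapacity.** A reader might infer that every patient will fall into the shorter category by construction. The documents do not support that. They do not say when the count starts, so absence that began before the operation could pass 6 weeks by day 35. They also do not show the questionnaire, and an item asking for the certified or expected length of absence could be answered at day 35. Against this, the article mentions neither route and Table 3 describes resource use as postoperative. The objection limits the point to observed absence that starts at surgery; it does not remove it. It is also fair that this is one conditional item in a descriptive assessment, listed after the nine numbered secondary endpoints, and that no efficacy or safety conclusion depends on it.

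**On Visit 5.** A reader might infer that about half the patients lack primary-endpoint information and that the day-90 estimate is under threat. That goes too far. The nominal visit is on day 90. The one-half figure comes from assuming an even spread of visits; the article reports no visit timing. Patients seen early are censored, the article names Kaplan-Meier estimation for partial follow-up, and with double blinding visit timing should not depend on arm. Provided censoring is unrelated to risk and some patients stay under observation to day 90, the estimate remains valid. An event near day 90 does carry more weight, but the overall cost in precision is the 2% above. What stands is that censoring does not recover an event on days 81 to 90 after an early final visit.

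**Conclusion.** The work-incapacity point holds as an internal inconsistency. Three places in the article fix collection at day 35, Table 2 extends it to day 42 at most, and the category needs more than 42 days. For absence starting at surgery, the upper category cannot be observed. This rests on calendar arithmetic alone, and nothing in the article reconciles it. The number of patients affected cannot be given, because the article states neither the share in employment nor the usual length of absence.

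The Visit 5 point is literally true but minor: 0.03 percentage points with evenly spread visits and 0.11 at the very most, against a non-inferiority margin of 1.0 point. These figures assume a constant hazard and a 1% rate in both arms.

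The first point is worth correcting because the plan cannot measure one of its named parameters as written and the remedy is cheap. The second is a tidy-up.

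**What to change.** 1. Ask the work-incapacity duration item at Visit 5, where two patient questionnaires are already completed, and exempt it from the day-35 limit in Outcomes and Table 3. Alternatively, keep it at Visit 4 with a cut-off that day 35 can observe, such as whether the patient is still unable to work on that day. State when the count starts and, if certified or expected duration is what is meant, say so. The cost is one questionnaire item and a small amendment.

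2. Schedule the final contact at day 90 to 100. This halves the window from 20 to 10 days for an on-site visit, with some added risk of visits out of window. A lighter option is to leave the visit at day 90 ± 10 and add a short event-status query at day 90 to 100 for patients seen earlier; Visit 4 is already done by telephone.

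No extra readmission question is needed, since readmission within 3 months is already a secondary endpoint. At the last reported count (March 2025), 59 of 2,932 planned patients were enrolled (59/2,932 = 2.0%), so a change at that stage would have covered nearly the whole trial. The present count is not known from the article.
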